**Figure 6 F6:**
[figure not shown]
**Detailed study design**.

Data collection for Theme 1 will be based on extraction from existing operational information systems in a variety of health and social care settings. This requires not only the extraction of large population-based data sets, but also a method to link data using a pseudoanonymised identifier which protects an individual's identify in accord with national guidance.

### Population

#### (a) *Patients with long-term health conditions*

Three clinical conditions were included in the study: heart failure; diabetes and COPD. In the interests of maximising external validity in this pragmatic trial, eligibility was not conferred on the basis of formal clinical assessment of disease severity (e.g. HbA1c, FEV1 % predicted, brain natriuretic peptide test). Instead patients were deemed eligible on the basis of either (i) their inclusion on the relevant Quality Outcomes Framework (QOF) register in primary care, (ii) a confirmed medical diagnosis in primary or secondary care medical records as indicated by GP Read Codes or ICD-10 codes, or (iii) confirmation of disease status by a local clinician (i.e. GP, community matron) or by their hospital consultant. Patients were not excluded on the basis of additional physical co-morbidities.

#### (b) Individuals with social care needs

Inclusion criteria were informed by the Department of Health Fair Access to Care criteria, and included people aged 18+ meeting one or more of the following criteria: currently in receipt of, or considered to have a need for night sitting; receiving 10 or more hours per week of home care; receiving 1 or more days per week of day care; mobility difficulties; those who have had a fall or who are considered at high risk of falling; a live-in or nearby carer facing difficulties carrying their current burden of responsibilities; or cognitive impairment/confusion with live-in or nearby carer.

### Interventions and comparisons

The evaluation is designed as an assessment of the value of two types of telemonitoring technology broadly characterised as telehealth and telecare. Each site has separate agreements with technology suppliers and there is no attempt to standardise the exact technology across sites. The analysis plan does not propose to evaluate the effects of individual technologies and the study is not powered to do so.

#### (a) Telehealth and telecare

Telehealth participants in Cornwall and Kent received a home monitoring system comprising a base unit (the *Tunstall RTX 3370 *or the *Viterion V100 *respectively), which is a small device with an LCD screen and response buttons to allow navigation of symptom questions and educational messages to be transmitted to participants, together with up to four peripheral monitoring devices. In Newham, telehealth participants received the Philips Motiva Personal Healthcare System comprising a set top box that connects to a television allowing symptom questions, educational videos and a graphical history of recent clinical readings to be accessed via a dedicated channel, plus an equivalent range of peripheral monitoring devices. Sites used different protocols for allocating peripheral devices but across all sites the critical devices by condition were a pulse oximeter (for COPD), a glucometer (for diabetes) and weighing scales (for heart failure). Participants with multiple conditions received multiple peripheral devices. Participants were asked to take clinical readings up to 5 days per week at the same time each day but the frequency was adjusted according to their individual history (e.g. a participant with diabetes and well controlled blood glucose would be asked to take readings less frequently than one with poorly controlled blood glucose). In Cornwall and Newham the base unit or set top box provided a visual and audio reminder when readings were due. At the end of each session data from clinical readings and symptom questions were sent to a monitoring centre via a secure server either automatically (in Cornwall and Newham) or following participant authorisation (in Kent).

Across all sites, telecare participants received a *Tunstall Lifeline Connect *or *Connect+ *base unit and pendant alarm together with any number of 27 peripheral devices classified into four broad categories: personal health and well-being sensors (e.g. bed/chair occupancy sensors, enuresis sensor, epilepsy sensor, fall detector, medication dispenser), sensory impairment aids (e.g. big button telephone, wearable vibrating alert), safety and security aids (e.g. bogus caller button, key safe) and environmental monitoring sensors (e.g. carbon monoxide detector, heat sensor, flood detector). Peripheral telecare devices were allocated on the basis of a needs assessment and participants with multiple needs were allocated appropriate combinations of peripheral devices. Telecare is primarily a passive system to monitor behaviour (via sensors around the home), facilitate independent living (via aids for memory, safety and sensory impairment) and raise alarms either automatically (via sensors) or manually (via a personal alarm or pull cord) in the event of an emergency. As such there was no required behavioural regimen that telecare intervention participants were expected to adhere to (i.e. they were not expected to take any clinical readings or answer symptom questions on a regular basis via the base unit or set top box). Data from sensors and alarms were automatically sent to a monitoring centre via a telephone line.

Monitoring centres were staffed by specialist nurses and community matrons. Incoming telehealth readings were automatically classified using a traffic light system of red, amber or green alerts based on relevant NICE guidelines or on individually tailored criteria specified by clinicians familiar with the case history. Red alerts in telehealth usually represent an opportunity for early intervention to prevent or minimise imminent clinical deterioration (e.g. titration of medications in response to a sudden weight change in heart failure may prevent critical exacerbation of symptoms and avoid the need for more costly and/or more risky treatments). Incoming data from certain telecare sensors (e.g. fall detector, heat sensor, smoke alarm) generated a red flag if outside set parameters to indicate a potential emergency situation requiring an immediate response. Other telecare sensors (e.g. bed/chair occupancy sensors) generated more ambiguous information and usually required contact with the user to establish their status. Telehealth alerts were typically monitored during office hours on a daily basis (Monday to Friday), while telecare alerts were monitored 24 hours per day, 365 days per year. Monitoring centre staff provided a stepped-care response to alerts ranging from reviewing recent clinical readings but taking no further action or requesting a repeat reading (these responses are for telehealth only) through to contacting the participant via the base unit or telephone, visiting the participant or referring on to another healthcare professional (e.g. GP, secondary care services or emergency services).

#### (b) Waiting list controls

Telehealth and telecare participants randomised to the control arm received standard health and social care for 12-months and then, subject to re-assessment, were offered telehealth or telecare at the end of trial.

### Outcomes

Theme 1 will collect and link large, administrative datasets with the aim of tracking service use for (a) up to three years pre-intervention and (b) 12 months post- intervention. It will include an assessment of hospital utilisation, including emergency and elective inpatient admissions, inpatient bed day use, outpatient attendances and accident and emergency visits; primary care utilisation, including GP encounters, prescription drugs and community matron visits; and, if possible, social care utilisation such as the use of domiciliary and residential care. Costs will be attributed to activity using national Payment by Results tariffs and reference costs.

Theme 2 and 3 include a comprehensive assessment of PROMs and health utilisation measures at 3 and 12 months, including general quality of life [14-16], disease-specific quality of life (teleheath only) [17-19], psychological well being [20,21], perceived acceptability of telemonitoring devices; use of telehealth and telecare; attitudes, self-efficacy and self-care behaviours [22-25], clinical outcomes (for telehealth participants), social networks [26], illness burden [27], disability [28,29] and health care and social services utilisation [30,31]. Carer outcomes include carer anxiety and caregiver strain [32,33], and carer costs include carer time spent in providing care to the participant as well as lost productivity. The full range of assessment instruments is provided online (Additional file 1).

### Sample size calculation

#### (a) Sample size calculation for Theme 1

The primary outcome measure was taken as the proportion admitted to hospital, with the secondary outcome measure being number of bed days. It was thought important to be able to detect a relative change in admission proportion of between 15% and 20%, from a baseline of 25% (estimated from actual site data), and a change in bed day use of 20%, both at power of 80% and two-sided p-value of < 0.05. Previous studies in the older population suggested that the intra cluster correlation (ICC) for admissions would be around 0.001 [34]. Sample size calculations were carried out using appropriate formulae [35] and suggested that a sample of 3,000 patients would allow the detection of a relative risk reduction (RRR) of 17.5% in admission proportion and a 20% reduction in bed days using the above criteria. Given that two separate RCTs of telehealth and telecare were being run, this means that the overall target sample size for Theme 1 was 6,000 patients.

#### (b) Sample size calculation for Theme 2 and 3

The sample size requirements were calculated in relation to COPD using the most plausible condition-specific health related quality of life measure: the Chronic Respiratory Questionnaire (CRQ) and its key dimension (the dyspnoea scale). Baseline mean scores were estimated at between 2.3 and 3.3 with a standard deviation of 1.0 [36]. Taking the minimal clinical important difference (MCID) at a conservative 0.3 [37], the effect size (given the observed baseline SD of 1.0) would be 0.3. Since ICC values of around 0.03 for both morbidity [38] and health related quality of life [39] variables have been reported, the ICC was estimated at 0.01 and 0.05. With power of 80% and two-sided p-value of < 0.05, the required sample size would be between 200 and 300 per condition (i.e. an overall sample size of 900), assuming the effect size for the health related quality of life measures is around the same level of 0.3 for the other conditions.

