### Analysis

The overall trial essentially involves two nested trials (one comparing telehealth with usual care, and one comparing telecare with usual care) which will be analysed separately but using identical procedures.

Unlike other evaluations of technologies in the NHS [40], the trial is not primarily designed to assess the effectiveness of any particular type of telecare or telehealth technology, and the primary analysis is at the level of the technology type (i.e. telehealth or telecare). There are no plans to conduct analyses of individual technologies.

#### (a) Themes 1 and 3

Baseline characteristics (e.g. age; sex; ethnicity; co-morbidities; risk of hospitalisation; typical hospital use) of the patients in the intervention and usual care arms will be compared and adjusted for where appropriate. Utilisation (inpatient admissions, bed day use, and cost) will be compared between the two groups for the three years before each patient receives the intervention, and the 12 months afterwards using appropriate statistical models for cluster randomised trials.

One method of analysing the results of Theme 1 will be using a risk stratification tool, to identify individuals at different levels of risk of future hospitalisation. Two such tools will be used, the Patients At Risk of Rehospitalisation (PARR) model and the Combined Predictive Model.^2 ^Both of these models are in use in the NHS to case-find patients for admission-avoidance programmes. The aim will be to understand which patients saw greatest changes in service use from the addition of telehealth or telecare, according to standard metrics used routinely to target services in parts of the NHS.

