Clinical effectiveness (quality of life, well-being, self-care, and carer burden) at 3 and 12 months will be compared between the groups, taking into account scores at baseline, and adjusting for potential confounders where appropriate, using statistical models suitable for cluster randomised trials.

The telehealth trial involves three separate clinical populations, and we will assess the differential impact of telehealth in these different clinical populations using a pre-specified subgroup analysis across conditions (including a group with co-morbidities).

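### The stated inputs for Themes 2 and 3 do not give 80% power with 200 to 300 patients per condition: about 350 are needed before clustering, and 900 overall falls short of 1,050

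*Protocol article*

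**What the plan says.** The protocol article, Sample size calculation, part (b), sizes Themes 2 and 3 on the dyspnoea scale of the Chronic Respiratory Questionnaire in COPD. The inputs are:

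- Variability: "Baseline mean scores were estimated at between 2.3 and 3.3 with a standard deviation of 1.0".
- Target difference: a minimal important difference of 0.3, so that "the effect size (given the observed baseline SD of 1.0) would be 0.3".
- Clustering: "the ICC was estimated at 0.01 and 0.05".
- Result, at 80% power and two-sided 5% significance: "the required sample size would be between 200 and 300 per condition (i.e. an overall sample size of 900"), on the assumption that an effect of about 0.3 also applies in the other conditions.

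The Population section says "Three clinical conditions were included in the study: heart failure; diabetes and COPD". The figure of 900 is therefore 3 x 300.

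In the Analysis section, "the primary analysis is at the level of the technology type (i.e. telehealth or telecare"). For Theme 2 the article plans models that account for baseline scores, and a "pre-specified subgroup analysis across conditions (including a group with co-morbidities"). Part (b) does not say whether 200 to 300 is per arm or in total, and gives neither a cluster size nor a baseline correlation.

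**The concern.** The 80% power is attached to each condition, but the printed inputs and the printed result disagree. Two arms compared at an effect size of 0.3 need more than 300 patients even if practices had no clustering effect, and the plan assumes that they do. Read as a two-arm total, the whole range of 200 to 300 lies below the unclustered minimum.

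The stake is interpretation. The article pre-specifies an analysis by condition. A reader who relies on the 80% could take a null result in COPD, diabetes or heart failure as good evidence against a difference of 0.3 SD, when the chance of detecting that difference was materially lower than stated.

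**Working it through.** **Inputs.** From Sample size calculation (b): difference 0.3, SD 1.0, power 80%, two-sided 0.05, ICC 0.01 and 0.05. From Population: three conditions. Assumed, because not stated: equal arms (the most favourable split) and m patients per practice, shown at 5 and 15. No attrition is applied.

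**1. Trying to reproduce the plan's figure as a total, without clustering.**

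n per arm = 2 x (1.96 + 0.8416)² / 0.3² = 174.4, rounded up to 175. That is 350 per condition and 3 x 350 = 1,050 overall. Neither 200 nor 300 is reproduced.

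**2. Trying to reproduce it as a per-arm figure.**

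With design effect DE = 1 + (m - 1) x ICC and m = 15:

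- ICC 0.01: DE = 1.14, and 174.4 x 1.14 = 199
- ICC 0.05: DE = 1.70, and 174.4 x 1.70 = 297 (296.5 before rounding up)

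One cluster size matches both ends. Working backwards, n(1 + 0.01x) = 200 and n(1 + 0.05x) = 300 give n = 175 and x = 14.3, so m is about 15. On this reading the requirement is 400 to 600 per condition, or 1,200 to 1,800 overall.

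**3. Trying to reproduce it as a baseline-adjusted total.**

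Total = 2 x 174.4 x (1 - r²) x DE. With r = 0.7 and m = 15:

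- ICC 0.01: 348.8 x 0.51 x 1.14 = 203
- ICC 0.05: 348.8 x 0.51 x 1.70 = 302

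This also matches, but r appears nowhere in the article. With r = 0.5 and m = 15 the totals are 298 and 445, so the upper end is not reproduced.

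**4. Power if 200 to 300 is a two-arm total, unadjusted.**

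Power = Φ(0.3 x √(n per arm / (2 x DE)) - 1.96). For 150 per arm without clustering: Φ(0.3 x √75 - 1.96) = Φ(0.638) = 73.8%.

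| Patients per practice | ICC | DE | Power, 300 total | Power, 200 total |
|---|---|---|---|---|
| no clustering | – | 1.00 | 73.8% | 56.4% |
| 5 (assumed) | 0.01 | 1.04 | 72.2% | 54.8% |
| 5 (assumed) | 0.05 | 1.20 | 66.0% | 49.1% |
| 15 (assumed) | 0.01 | 1.14 | 68.2% | 51.1% |
| 15 (assumed) | 0.05 | 1.70 | 51.3% | 37.0% |

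**5. Detectable effect at 80% power, 150 per arm.**

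2.8016 x √(2 x DE / 150):

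- no clustering: 0.32 SD
- m = 5: 0.33 to 0.35 SD
- m = 15: 0.35 to 0.42 SD

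**6. Pooled telehealth comparison, 450 per arm, effect 0.3.**

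If conditions are spread evenly over practices, the pooled cluster is about three times the per-condition one.

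- 15 pooled (about 5 per condition): DE 1.14 and 1.70, power 98.8% and 93.2%.
- 15 per condition (about 45 pooled): DE 1.44 and 3.20, power 96% and 71%.

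**The case against.** **The per-arm mix-up is not proven.** A reader might infer from step 2 that a factor of two was certainly lost. The text never says per arm or total, two rounded endpoints are suggestive only, and a baseline correlation near 0.7 fits equally well. The article does plan to adjust for baseline, and the figures that might show arm-level targets are not available here. This stands: the cause is an inference. It does not clear the text, because part (b) states no correlation and derives the effect size from the plain SD of 1.0. If a correlation was used, a decisive input is missing from a calculation whose other inputs are printed.

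**Power near 51% is the worst corner.** It needs 15 patients per practice, ICC 0.05 and no adjustment. With 300 in total, r = 0.5 and 5 per practice, power would be 84% (ICC 0.01) and 78% (ICC 0.05); with r = 0.6 it would be 89% and 84%. This also stands. The range 51-68% is conditional on a cluster size that the article does not give, so it cannot be presented as the plan's power.

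**The primary analysis is by technology type.** Conditions are a subgroup analysis, and pooling gives far more power. That limits the consequence. It does not make the sentence true: the 80% is claimed per condition, on a COPD-specific scale that cannot be pooled across conditions.

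**Conclusion.** The per-condition power statement is wrong as written if 200 to 300 is a two-arm total. From the printed inputs alone, an unadjusted comparison has at most 74% power at 300 and 56% at 200, and 900 lies below the unclustered requirement of 1,050. These bounds assume only two equal arms; unequal arms would lower them. Anything more specific depends on an assumed cluster size: at 300 per condition, 66-72% with 5 per practice and 51-68% with 15.

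Three stronger readings are not supported. First, that the authors certainly took a per-arm figure for a total: this is likely, but the baseline-adjusted reading remains open. Second, that the telehealth trial is underpowered for its main comparison: pooled power at 0.3 SD is 93-99% with 15 patients per practice pooled and 71-96% with about 45, so only the last corner falls below 80%. Third, that telecare, attrition or the co-morbid group reveal further shortfalls: a condensed article may leave these to the full protocol, and it does not say how large the co-morbid group is or whether it would reduce the others.

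**What to change.** In Sample size calculation (b):

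1. State whether 200 to 300 is per arm or in total, and give the cluster size and any baseline correlation used.
2. Unless a correlation is stated and justified, replace the 80% per-condition claim for 900 patients with the power delivered: at most 74% at 150 per arm, lower with clustering. Give the matching detectable effect: at least about 0.32 SD before clustering, about 0.33-0.35 SD at 5 per practice and 0.35-0.42 SD at 15.
3. Present results by condition as estimates with confidence intervals.
4. If a power is claimed for the pooled telehealth comparison, tie it to a measure that all conditions complete, and use a pooled cluster size consistent with the per-condition one.

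The cost is rewording, with no extra patients. The downside is a less favourable stated power within each condition.

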### Trial procedures

General practices were approached by letter inviting them to take part in the trial. Once a practice had consented, potential participants for telehealth were identified in each site using existing registers of patients with long-term conditions in general practice. Potential participants for telecare in each practice were identified from databases held by social services departments.

To meet ethical obligations, patients were asked to complete and return a 'data sharing letter' if they consented to their data being shared with the research team. Once this letter was received, patients received a 'light touch' visit from a member of the project team in each site, where consent was taken to (a) participate in the main trial (Theme 1) and (b) the questionnaire study (Themes 2 and 3).

Participants who agreed to take part in the Themes 2 and 3 were subsequently contacted by a market research company to arrange a convenient time for the baseline interview. At this interview, patients received information about this part of the study and signed consent. The baseline assessment varied by participant status (i.e. COPD, heart failure, diabetes, telecare, carers) but each comprised a core of standardised PROMs. The PROMs were self-completed by the participant with the researcher on hand to explain or clarify. Data on health care utilisation were collected via interview. The average total time for assisted baseline interview completion was 80 minutes.

Carers of service users in the trial were identified by sites usually at the 'light touch' visit, either by the carer expressing an interest or via *snowball sampling *(i.e. asking participants if they had an informal carer at the baseline interview).

Each practice was allocated to groups via a centrally administered minimisation algorithm. The allocation determined the technologies available to each practice (i.e. either telehealth or telecare) and their associated patients. Following installation of the technologies, participants will be followed-up for 12-months. After 12-months, the 'usual care' groups were eligible to receive the appropriate interventions.

### Analysis

The overall trial essentially involves two nested trials (one comparing telehealth with usual care, and one comparing telecare with usual care) which will be analysed separately but using identical procedures.

Unlike other evaluations of technologies in the NHS [40], the trial is not primarily designed to assess the effectiveness of any particular type of telecare or telehealth technology, and the primary analysis is at the level of the technology type (i.e. telehealth or telecare). There are no plans to conduct analyses of individual technologies.

#### (a) Themes 1 and 3

Baseline characteristics (e.g. age; sex; ethnicity; co-morbidities; risk of hospitalisation; typical hospital use) of the patients in the intervention and usual care arms will be compared and adjusted for where appropriate. Utilisation (inpatient admissions, bed day use, and cost) will be compared between the two groups for the three years before each patient receives the intervention, and the 12 months afterwards using appropriate statistical models for cluster randomised trials.

One method of analysing the results of Theme 1 will be using a risk stratification tool, to identify individuals at different levels of risk of future hospitalisation. Two such tools will be used, the Patients At Risk of Rehospitalisation (PARR) model and the Combined Predictive Model.^2 ^Both of these models are in use in the NHS to case-find patients for admission-avoidance programmes. The aim will be to understand which patients saw greatest changes in service use from the addition of telehealth or telecare, according to standard metrics used routinely to target services in parts of the NHS.

Data on health, social care and other support service use for participants will be collected using the CSRI [30]. Unit costs will be attached to service use data to calculate a total cost per patient at baseline, 3 months and 12 month follow up. Costs will be calculated on the basis of the costs incurred in the 3 months prior to the 3 data collection points. Service use and associated costs for participants in both trial arms will be reported under sub-categories such as use of acute hospital services and community social services. All cost categories will be allocated to a perspective (whether NHS, Local authority, NHS and Local authority, or public sector). The costs of the intervention will be calculated specifically for this study from data provided by the sites and those costs attached to participants receiving the intervention in the telehealth and telecare groups. Point estimates of the costs for the control and intervention groups in each trial arm will be derived from univariate and multivariate analyses of costs from all 4 perspectives.

The effectiveness of the telehealth and telecare programmes will be compared using a common unit of outcome measurement, the QALY, to be constructed from the EQ-5D health state classification [16] scored using established algorithms (York Tariff) [41]. QALY scores will be calculated for the baseline, 3 month and 12 month follow-up points. In addition, scores from a broader measure of quality of life intended for health and social care evaluations, the ICECAP [14], will be examined. ICECAP scores at each time point will be presented for all three time points. Incremental cost effectiveness ratios (ICER) will be calculated at the 3 month and 12 month follow up points for both trial arms. The ICER will be defined as the difference in mean costs incurred by the treatment groups in each arm over the previous 3 month period, divided by the difference in mean QALY gain between those treatment groups. A cost-effectiveness acceptability curve (CEAC) will be produced, based on the results of a model of net monetary benefit for clustered data. The CEAC allows the decision-maker to see what is the likelihood of telehealth and telecare being cost-effective at different monetary values of increments of improvement in the chosen outcome.

#### (b) Theme 2

Clinical effectiveness (quality of life, well-being, self-care, and carer burden) at 3 and 12 months will be compared between the groups, taking into account scores at baseline, and adjusting for potential confounders where appropriate, using statistical models suitable for cluster randomised trials.

The telehealth trial involves three separate clinical populations, and we will assess the differential impact of telehealth in these different clinical populations using a pre-specified subgroup analysis across conditions (including a group with co-morbidities).

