**Figure 5 F5:**
[figure not shown]
**Theme 5**.

Themes 1-3 were all based on the same core trial design and involved the same population criteria and interventions, but the samples and outcome assessments differed. The core measure of service utilisation in Theme 1 was use of hospital services, to support a business care for the adoption of telemonitoring technologies in the United Kingdom. Due to the large skew in distribution of hospital use, a large sample of patients were required (see sample size calculation below). Therefore, all patients who receive telecare or telehealth in the practices involved in the evaluation were to have routine data on health and social care service extracted from existing data sources. This did not require the individual patient assessments required for Themes 2 and 3. Themes 2 and 3 used a subsample of patients who were assessed using patient reported outcome measures (PROMs) and health utilisation measures to provide a more comprehensive assessment of clinical and cost-effectiveness. The design is shown in more detail in Figure 6.

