The themes address related issues using a range of methods. For example, Theme 1 exploits large, existing sources of administrative data on service use while Theme 3 collects self-reported data from patients. Several studies have compared health care utilization as described in administrative and self-reported data [45,46]. These have typically found significant differences, especially for people with high levels of use, older people, and for people with poor health status. The trial is also novel in the ways that it exploits data linkage across a range of operational data sets. The advantages of this approach are that it allows the team to access large volumes of computerised data relatively cheaply. This enables analyses of much larger groups but also includes historical data which can be used for risk adjustment and sub-group analyses. The disadvantages are that the data in administrative systems may be of poor quality and it may not capture the most important variables. The combination of administrative data (Theme 1), and directly recorded patient events (Theme 3) provide an opportunity to test whether data problems create different results.

The potential of telehealth and telecare technology to improve care and reduce costs is limited by a lack of rigorous evidence of actual impact. If telehealth and telecare technology proves cost-effective in our trial, it will provide additional options for health services worldwide to deliver care for populations with high levels of need.

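### Theme 3 costs no service use in months 3–9 of follow-up, and the 12-month cost-effectiveness ratio rests on months 9–12 alone, although Theme 1 records hospital use for the whole year

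*Protocol article*

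**What the plan says.** The Analysis section on Themes 1 and 3 attaches unit costs to questionnaire data (the CSRI) to "calculate a total cost per patient at baseline, 3 months and 12 month follow up". It fixes the recall period: "Costs will be calculated on the basis of the costs incurred in the 3 months prior to the 3 data collection points". The ICER is calculated at months 3 and 12, and its numerator is "the difference in mean costs incurred by the treatment groups in each arm over the previous 3 month period". The section mentions no interpolation, annualisation or other route to a full-year cost.

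Trial procedures sets the length of follow-up: "Following installation of the technologies, participants will be followed-up for 12-months".

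Theme 1 uses administrative records instead. Under Outcomes these are meant for "tracking service use for (a) up to three years pre-intervention and (b) 12 months post- intervention", and they include admissions, bed days, outpatient attendances and emergency department visits. Social care use is to be added only if possible. The Methods/Design text on the samples says that "Themes 2 and 3 used a subsample of patients", so Theme 1 records should exist for the same people.

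The Discussion, under advantages and disadvantages of the design, says that the two sources together "provide an opportunity to test whether data problems create different results".

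**The concern.** Cost-effectiveness and acute hospital use and costs are among the stated aims of the trial. Hospital use is skewed, as the article itself notes, so relatively few patients and episodes drive a mean cost. A cost estimate that leaves out half of the follow-up year discards a large share of those episodes. The ICER labelled 12-month uses only the last quarter and discards more.

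The season that is observed also depends on when a patient started. Conditions such as COPD may have seasonal admissions, so the level of cost seen in a window can differ from the yearly level. Multiplying a window up to a year would not remove that.

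The missing hospital months are already to be collected for Theme 1. The gap in Theme 3 is a choice of source and not a limit of the data.

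**Working it through.** No figure in the plan corresponds to this check, so there is nothing to reproduce first.

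**Months covered**
- Data collection points: baseline, 3 and 12 months. Recall: 3 months each.
- Windows relative to the start: −3 to 0, 0 to 3, and 9 to 12.
- Follow-up months covered: 3 + 3 = 6 of 12. Months 3–9 are uncovered.
- Months used in the ICER at 12 months: 3 of 12.

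**Admissions seen**
- Inputs: 25% admission proportion and 900 participants, both from Sample size calculation.
- Assumptions: the 25% is annual (the article does not say so), the hazard is constant, recall is perfect, and the proportion carries over to the Theme 2 and 3 subsample.
- Annual hazard: h = −ln(1 − 0.25) = −ln(0.75).
- Both follow-up windows (6 months): 1 − exp(−h/2) = 1 − 0.75^0.5 = 13.4%.
- Last window (3 months): 1 − exp(−h/4) = 1 − 0.75^0.25 = 6.9%.

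| Period | Patients with an admission | In 900 patients |
|---|---|---|
| Full 12 months | 25% | 225 |
| Months 0–3 and 9–12 | 13.4% | about 121 |
| Months 9–12 only | 6.9% | about 62 |

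**Season**
- On the calendar, months 0–3 and 9–12 after the start form one six-month block centred on the start date. The baseline window covers the same calendar months as 9–12, one year earlier, so it adds no new season.
- The article gives neither start dates nor a seasonal pattern. I assumed a cosine pattern with amplitude A of 10% to 30% of the yearly mean rate.
- Largest error in the mean rate, for the least favourable single start date:
  - both windows: A × 2/π, which is 6%, 13% and 19% for A = 10%, 20% and 30%;
  - last window only: A × sin(π/4)/(π/4), which is 9%, 18% and 27%.
- Averaged over start dates spread evenly through the year, the error is zero.

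How much of winter is seen also depends on how winter is defined:

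| Winter taken as | Start dates seeing all of it | None of it | Part of it |
|---|---|---|---|
| December–February | 25% | 25% | 50% |
| November–February | 17% | 17% | 66% |
| October–March | only a 1 January start | only a 1 July start | about 99% |

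**Comparing the two sources**

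A simulation with events spread evenly over the year gave these ratios of self-reported to administrative use:

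| Under-reporting | Same windows | Against the 12-month total |
|---|---|---|
| none | 1.00 | 0.50 |
| 20% | 0.80 | 0.40 |

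Matching the windows isolates reporting error. Comparing with a yearly total mixes it with the gap.

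**The case against.** **No bias between arms is shown.** Season acts on both arms, and over evenly spread start dates the error in level averages out. A reader might infer that the arm contrast is biased. That needs start dates that differ by arm. The clock is described from installation, which waiting-list controls do not have during the 12 months, and the article gives no start date for controls. Equal timing therefore cannot be confirmed, but nothing in the text shows a difference. This objection stands.

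**Winter is not simply seen or missed.** A reader might infer that each patient's winter use is observed wholly or not at all. The table above shows that this holds for about half of start dates with a December–February winter and for almost none with an October–March winter.

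**The cross-check is not defeated.** A reader might infer that comparing Theme 1 with Theme 3 cannot separate reporting error from the uncovered months. The administrative span contains every questionnaire window, so the records can be cut to match, provided that they carry event dates. The Discussion prescribes no comparison with yearly totals. How to match the windows is ordinary analysis-plan detail.

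**The admission proportion is a Theme 1 outcome.** Theme 3 estimates mean cost per window and claims no annual proportion. This is correct. The 13% and 7% indicate how much information the windows hold and are not an error in a reported result. The plan also does not double the observed half-year, so no error from doing so can be charged to it.

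**Replacing self-report loses an independent source.** This is fair, and it is why both results should be reported.

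The stated rule itself remains: costs come from 3-month windows, and the text gives no way to a 12-month cost.

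**Conclusion.** The point holds in a limited form. As written, Theme 3 costs 6 of the 12 follow-up months, and the ICER at 12 months uses 3 of them. If the 25% is annual and the hazard constant, the windows catch about 13% and 7% of patients with an admission, against 25% over the year.

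The consequence is a cost difference resting on fewer events and on the calendar months that happen to be covered. For a single start date, and under assumed amplitudes of 10% to 30%, the yearly rate could be misstated by at most 6% to 19% from both windows, or 9% to 27% from the last one. These are extremes for one start date and not estimates for the trial mean.

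The documents support neither a claim of bias between arms nor a claim that the planned comparison of sources must fail. The case for change is that a fuller measure of hospital use is already due to be collected for the same people.

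**What to change.** 1. For Theme 3 participants, calculate hospital use and cost over the full 12 months from the Theme 1 administrative records, and use these in the cost-effectiveness analysis at 12 months. This depends on linking those records person by person to the questionnaire data. The article describes linkage across operational systems by a pseudonymised identifier but does not explicitly include the questionnaires, so this must be confirmed first.
2. Report this result beside the CSRI-based one, so that the self-report source is kept.
3. Use the CSRI for services that the administrative data do not hold, with season of start as a covariate. State that months 3–9 are not observed for those services.
4. For any comparison of Theme 1 with Theme 3, use the same people and the same windows.

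The cost is analysis-plan wording and some additional data cutting, with no new patients, visits or data collection if the linkage is in place. The small downside is that hospital costs and other costs then come from different sources.
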